#### Procedure*.*

Testing will be conducted in a calm lab environment, and the infants will be fed and have a dry diaper before the equipment is applied. Before testing, the researchers will guide the mothers verbally on how to sing a song of their own choice, which can be a song of kin that is a personalized song meaningful to the mother aiming to foster bonding, reduce stress, and improve physiological stability in infant and mother, or a traditional children’s play song. The mother is instructed to hum and sing with or without words in a positive, joyful expressive affect in her prosody, using a steady, repetitive and predictable pulse in her song, singing with a smiling exaggerated expression in her face to capture her infant’s attention, striving to establish a mutual gaze and eye-to-eye interaction with her infant, accentuating the singing rhythm in her affectionate touch (if applicable), overall to sensitively adjust and match her singing style and her multimodal communications (auditory-prosodic, visual-facial, and tactile-gestural nonverbal communications) to her infant’s cues, responses, and state, aiming to create a positive affect in the dyad with her interactive multisensory stimulation and regulation. The equipment is first attached to the mother and then to the infant, ensuring good signal quality and minimizing disturbance of the infant. To synchronise measurements (fNIRS, SC, HRV, eye tracking, and video) we will verbally announce the time-points 1–7, and simultaneously manually mark the events in the equipment with keyboard markers (Fig 1). The mother and infant will then sit together in a comfortable chair in skin-to-skin position for baseline registration lasting 5 minutes (1). When we have steady-state signals and a stable baseline, the mother will start singing (2) and she continues singing for 3 minutes. After that, she offers the infant to breastfeed (3). After another 3 minutes, or until the baby has a good grip on the breast, a nurse will search for a vein (4) and perform the venepuncture (5), while the mother continues to sing and breastfeed until blood collection is ready (6). Finally, 5 minutes of signal will be registered after the blood sampling is finished (7). Before regular data collection begins, two pilot tests were conducted to calibrate the equipment and time intervals.

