**Fig 1 pone.0353856.g001:**
[figure not shown]
Timeline showing the procedures in the test-setting. The numbers indicate timepoints for markers in the recording equipment and subsequent data analysis: 1 start of recording, mother and infant sit skin-to-skin, 2 start of singing, 3 start of breastfeeding, 4 the nurse touches the infants arm to start searching for a vein, 5 punction of the skin, 6 the needle is removed, 7 end of recording. SC = skin conductance activity, HR = heart rate.

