### Measurements and instruments

*Cerebral hemodynamics* will be recorded using functional Near Infrared Spectroscopy (fNIRS). Both mother and infant will wear head caps with optodes (transmitters and detectors) connected to a NIRSport2 data acquisition module (NIRx Medical Technologies, Berlin, Germany). The optode montages are designed in NIRSite 2.0 software (NIRx Medical Technologies) and imported into the data acquisition software Aurora fNIRS (NIRx Medical Technologies). The optodes in the mother montage are set to cover the following regions of interest (ROIs): prefrontal, posterior frontal, parietal, and temporal regions of the brain including the right and left temporoparietal junction, to capture auditory and visual functions as well as emotional and social regulation activities between and within brains [13,40,45]. The infant cap montage will cover the whole head, i.e., synchrony in the same ROIs will be registered on both subjects. No previous findings on synchrony during mother-led pain alleviation exist but Bembich et al. found activation in mothers’ parietal cortex and infants’ superior motor/somatosensory cortex when the mother’s observed a heel prick [40]. On both mothers and infants, we will use 16x16 channels set-ups following the 10–20 EEG placement system [46] (Fig 2) and the mother montage will include short channels to compensate for artefacts from superficial blood flow.

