**Fig 2 pone.0353856.g002:**
[figure not shown]
Infant (left) and mother (right) montage of fNIRS-optodes. Red = transmitter, blue = detector, circle = short channel. The mother montage is set to cover the following regions of interest: prefrontal, posterior frontal, parietal, and temporal regions of the brain including the right and left temporoparietal junction. The infant montage will cover the whole head and thus the same regions.

Oxygenated haemoglobin and deoxygenated haemoglobin (Oxy-Hb & Deoxy-Hb) will be registered for all channels in real-time using Aurora fNIRS and stored on a computer. The sampling rate will be set between 5 and 10 Hz using multilevel illumination.

Electrodes for registration of heart- and respiratory rate in the mother will be connected via a NIRxWINGS module (NIRx Medical Technologies) and registered in Aurora fNIRS. The infant will be attached to ECG-electrodes connected to a patient monitor (Philips IntelliVue X3, Eindhoven, NL).

From the heart rate (HR) registration heart rate variability (HRV) will be calculated. Electrodes for registration of skin conductance activity (SC) will be attached to the palmar side of the hand of the mother and connected via a NIRxWINGS module and registered in Aurora fNIRS. The infant will wear electrodes to record SC on the sole of the foot. The signal will be registered in GSR recording software (MedStorm, Oslo, Norway).

Two video cameras will be used, one to record the mother-infant interaction, later used for microanalysis of the live singing and social interactions [47], and one directed on the infant’s face, for later pain-scoring with the Behavioral Indicators of Infant Pain (BIIP) [48]. The mother will wear Tobii Pro 3 eye-tracking glasses to record her gaze at the infant [27].

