### Data analysis plan

Recorded data will be analysed at the following specific time points, that may vary slightly due to signal quality but will be synchronized for mother and infant (fig 1):

baseline, when the mother and infant are settled comfortably, before the mother starts humming, approximately 2 minutes and 30 seconds after the marker,when the mother has started humming, approximately 2 minutes after the marker,when the mother has established active breastfeeding, approximately 2 minutes after the marker,when the nurse is searching for a vein, approximately 30 seconds after the marker,directly after the venipuncture needle penetrates the skin,approximately 30 seconds after the blood sampling is finished, andbefore data collection is finished, approximately 2 minutes and 30 seconds after the blood sampling is finished.

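### Speaking the marker aloud at the skin puncture puts a probable shared sound on the one read-out with no delay after its marker; mark time point 5 silently

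*Protocol article*

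**What the plan says.** All places are in the protocol article.

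- **Procedure.** To synchronise fNIRS, skin conductance (SC), HRV, eye tracking and video, "we will verbally announce the time-points" 1–7, and at the same moment the events are keyed by hand as markers in the equipment. The mother goes on singing and breastfeeding during the venepuncture.
- **Fig 1 legend.** The markers that matter here are "5 punction of the skin, 6 the needle is removed". Marker 4 is the nurse's first touch of the arm to look for a vein.
- **Data analysis plan.** Time point 5 is read "directly after the venipuncture needle penetrates the skin", with no offset. The time point before it is read "when the nurse is searching for a vein, approximately 30 seconds after the marker".
- **Measurements and instruments.** The regions of interest include the temporal and temporoparietal areas and are chosen partly "to capture auditory and visual functions as well as emotional and social regulation activities". One device to be synchronised is on the mother's head: "The mother will wear Tobii Pro 3 eye-tracking glasses to record her gaze at the infant".
- **Sample, setting and procedure.** Infants who failed the hearing screening are excluded, so those enrolled can be expected to hear.
- **fNIRS data analysis; SCA data analysis; Statistical analyses.** Oxy-Hb and Deoxy-Hb levels and SC are calculated at each time point. The primary hypothesis, interbrain synchrony, is analysed by wavelet transform coherence (WTC) and mixed models per region and time point.

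**The concern.** A voice in the room is an external event common to both members of the dyad. Spoken well before the read-out, it does little harm, because the response has died away by then. Spoken at the instant the read-out begins, it becomes part of what is measured.

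Time point 5 is the painful event that the study is about, and some of the measured regions were chosen because they respond to sound. There is one group and one condition, with no silent marker, sham marker or comparison procedure. If mother and infant both show a haemoglobin or SC change just after the puncture, the design cannot say how much of it answers the voice and how much answers the needle or the mother's regulation of her infant. The overlap cannot be removed once the recordings exist.

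**Working it through.** **1. Distance from spoken marker to read-out.** Inputs: the Data analysis plan for the offsets, the Fig 1 legend for the marker events, and Procedure for the announcement rule and the 5 minutes of recording after sampling.

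| Time point | Event at marker | Read-out relative to the nearest announcement |
|---|---|---|
| 1 | start of recording, skin-to-skin | about 150 s after |
| 2 | singing starts | about 120 s after |
| 3 | breastfeeding starts | about 120 s after |
| 4 | nurse touches arm | about 30 s after |
| 5 | skin puncture | about 0 s after |
| 6 | needle removed | about 30 s after |
| 7 | end of recording | about 150 s after sampling ends, so about 300 − 150 = 150 s before marker 7 |

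Only time point 5 has no separation.

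**2. Shift in mean level at time point 5.** The documents give neither the size of a response to a spoken word nor the length of the read-out window, so both are assumed. Take a standard double-gamma haemodynamic response, h(t) = g(t; 6) − g(t; 16)/6, where g(t; k) is the gamma density with shape k and unit scale, rescaled to a peak of 1. For a peak response of A (in SD of the signal),

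shift over a window of T seconds = A × mean of h(t) over 0 to T.

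| Window T | Mean of h | A = 0.5 SD | A = 1 SD |
|---|---|---|---|
| 10 s | 0.53 | 0.26 SD | 0.53 SD |
| 15 s | 0.352 | 0.18 SD | 0.35 SD |
| 30 s | 0.16 | 0.08 SD | 0.16 SD |
| 60 s | 0.08 | 0.04 SD | 0.08 SD |

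Delaying the infant's response by 1 s changes the 15 s mean only from 0.352 to 0.357. The result depends strongly on the window: going from 15 s to 30 s more than halves it. By 30 s, h is practically zero, so on this model the read-outs at time points 4 and 6 are spared.

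**3. Effect on coherence.** Independent 1/f signals for mother and infant were band-passed at 0.01–0.5 Hz as planned. A common double-gamma response was added at the event, 1 s later in the infant. Morlet WTC was averaged over periods of 4–32 s in a 30 s window, with 150 runs for each amplitude. At 0.5 and 1 SD the mean coherence hardly moved. At 2 SD, outside the assumed range, it rose from 0.31 to 0.36, about 0.5 SD of its run-to-run spread. A repeat with separately written code showed the same pattern.

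**4. Skin conductance.** No SC effect was calculated. The Introduction describes SC as a measure of arousal and stress, so a response to a sudden voice is plausible, but nothing in the documents allows it to be sized.

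**The case against.** The other side has good points, and most of them limit the finding.

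- **Audibility is inferred.** The protocol states the purpose of the announcement as device synchronisation and does not say that it is addressed to the dyad. This stands as a matter of wording. But the dyad sits in the same calm room, and the announcement is meant to serve video and glasses worn by the mother, so it is very likely heard.
- **The mother is already singing.** Both members receive continuous shared sound by design, and one spoken word adds to it. This stands as a reason to expect a modest effect. It does not remove the overlap, because the singing runs through the whole procedure whereas the announcement is a new event locked to the puncture.
- **A reader might infer that the voice warns the mother of the needle.** The text does not support this. The announcement accompanies the marker and is not said to precede the puncture. The mother is in any case forewarned from marker 4, when the nurse starts to search for a vein.
- **A reader might infer that the primary synchrony result is biased towards the hypothesis.** The simulation speaks against this: over the assumed range of 0.5–1 SD, coherence hardly moves.
- **A reader might infer that all seven time points are affected.** The offsets show otherwise; six of the seven read-outs lie about 30 s or more from any announcement tied to their own marker.
- **Spoken marks are useful.** Signals come from several separate recorders, and the Limitations section calls their synchronisation crucial. Silencing markers 2–6 would give up five common reference points for a problem that sits at one. This stands, and it is why the change should be confined to marker 5.

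**Conclusion.** The point holds for time point 5 only. Followed as written, the procedure places a probable shared sound on the puncture read-out, and nothing in the single-condition design separates a response to the voice from a response to the puncture or to co-regulation.

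Its size is unknown from the documents. Under an assumed voice response of 0.5–1 SD with a double-gamma shape, the Oxy-Hb level would shift by about 0.18–0.35 SD over 15 s or 0.08–0.16 SD over 30 s. The exposure is chiefly the Oxy-Hb and Deoxy-Hb levels and possibly SC at this time point. The primary coherence analysis is not shown to be at risk. This is a worthwhile small improvement to the recording routine and does not undermine the study.

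**What to change.** In Procedure, keep the spoken announcement at markers 1–4, 6 and 7. Mark time point 5 silently with the keyboard markers already planned, with the staff member at the keyboard cued by a silent signal out of the mother's view.

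Locate event 5 in the video and eye-tracking records by interpolation between the spoken markers on either side:

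video time of 5 = video time of 4 + (key time of 5 − key time of 4) × (video time of 6 − video time of 4) ÷ (key time of 6 − key time of 4).

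Six spoken alignment points remain. No equipment, sample size, analysis or clinical step changes. The cost is that one event is located by the aligned clock and not by voice, and that staff must coordinate silently once per session. According to the study timeline, recruitment starts in spring 2026 and ends in December 2027. The change should be made as early as possible, since recordings already taken cannot be corrected.

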**Fig 1 pone.0353856.g001:**
[figure not shown]
Timeline showing the procedures in the test-setting. The numbers indicate timepoints for markers in the recording equipment and subsequent data analysis: 1 start of recording, mother and infant sit skin-to-skin, 2 start of singing, 3 start of breastfeeding, 4 the nurse touches the infants arm to start searching for a vein, 5 punction of the skin, 6 the needle is removed, 7 end of recording. SC = skin conductance activity, HR = heart rate.

### Measurements and instruments

*Cerebral hemodynamics* will be recorded using functional Near Infrared Spectroscopy (fNIRS). Both mother and infant will wear head caps with optodes (transmitters and detectors) connected to a NIRSport2 data acquisition module (NIRx Medical Technologies, Berlin, Germany). The optode montages are designed in NIRSite 2.0 software (NIRx Medical Technologies) and imported into the data acquisition software Aurora fNIRS (NIRx Medical Technologies). The optodes in the mother montage are set to cover the following regions of interest (ROIs): prefrontal, posterior frontal, parietal, and temporal regions of the brain including the right and left temporoparietal junction, to capture auditory and visual functions as well as emotional and social regulation activities between and within brains [13,40,45]. The infant cap montage will cover the whole head, i.e., synchrony in the same ROIs will be registered on both subjects. No previous findings on synchrony during mother-led pain alleviation exist but Bembich et al. found activation in mothers’ parietal cortex and infants’ superior motor/somatosensory cortex when the mother’s observed a heel prick [40]. On both mothers and infants, we will use 16x16 channels set-ups following the 10–20 EEG placement system [46] (Fig 2) and the mother montage will include short channels to compensate for artefacts from superficial blood flow.

**Fig 2 pone.0353856.g002:**
[figure not shown]
Infant (left) and mother (right) montage of fNIRS-optodes. Red = transmitter, blue = detector, circle = short channel. The mother montage is set to cover the following regions of interest: prefrontal, posterior frontal, parietal, and temporal regions of the brain including the right and left temporoparietal junction. The infant montage will cover the whole head and thus the same regions.

Oxygenated haemoglobin and deoxygenated haemoglobin (Oxy-Hb & Deoxy-Hb) will be registered for all channels in real-time using Aurora fNIRS and stored on a computer. The sampling rate will be set between 5 and 10 Hz using multilevel illumination.

Electrodes for registration of heart- and respiratory rate in the mother will be connected via a NIRxWINGS module (NIRx Medical Technologies) and registered in Aurora fNIRS. The infant will be attached to ECG-electrodes connected to a patient monitor (Philips IntelliVue X3, Eindhoven, NL).

From the heart rate (HR) registration heart rate variability (HRV) will be calculated. Electrodes for registration of skin conductance activity (SC) will be attached to the palmar side of the hand of the mother and connected via a NIRxWINGS module and registered in Aurora fNIRS. The infant will wear electrodes to record SC on the sole of the foot. The signal will be registered in GSR recording software (MedStorm, Oslo, Norway).

Two video cameras will be used, one to record the mother-infant interaction, later used for microanalysis of the live singing and social interactions [47], and one directed on the infant’s face, for later pain-scoring with the Behavioral Indicators of Infant Pain (BIIP) [48]. The mother will wear Tobii Pro 3 eye-tracking glasses to record her gaze at the infant [27].

### Data management plan

All participants will be given a study-ID to preserve confidentiality. The key code will be stored in a secure way, separate from all other study data. All measurements, including neurophysiological data and video recordings, together with characteristics of the participants will be stored on a secure server, with access only for the researchers.

### Data analysis plan

Recorded data will be analysed at the following specific time points, that may vary slightly due to signal quality but will be synchronized for mother and infant (fig 1):

baseline, when the mother and infant are settled comfortably, before the mother starts humming, approximately 2 minutes and 30 seconds after the marker,when the mother has started humming, approximately 2 minutes after the marker,when the mother has established active breastfeeding, approximately 2 minutes after the marker,when the nurse is searching for a vein, approximately 30 seconds after the marker,directly after the venipuncture needle penetrates the skin,approximately 30 seconds after the blood sampling is finished, andbefore data collection is finished, approximately 2 minutes and 30 seconds after the blood sampling is finished.

#### fNIRS data analysis.

fNIRS data will be analysed using Satori fNIRS analysis software (NIRx Medical Technologies). For the preprocessing, we will perform channel rejection either based on CV (coefficient of variance from other channels) or SCI (scalp coupling index). We will apply temporal filtering with a bandpass at 0,01–0,5 Hz, and linear detrending to avoid eventual shift in the data. We will perform motion correction and spike removal using TDDR (temporal derivative distribution repair) and remove physiological noise with SSR (short channel regression). We will calculate OxyHB and deoxy-Hb at the specified time points 1–7 and regions of interest. The analysis of the interbrain neural syncrony will follow the method described by Nguyen et al. [20], using Wawelet Transform Coherence (WTC).

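### The 0.01 Hz high-pass removes nearly all of any sustained Oxy-Hb/Deoxy-Hb change before the singing, breastfeeding and recovery levels are read

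*Protocol article*

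**What the plan says.** Three stated choices in the protocol article meet here.

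- **Filter** (fNIRS data analysis): "We will apply temporal filtering with a bandpass at 0,01–0,5 Hz, and linear detrending to avoid eventual shift in the data".
- **Quantity taken from the signal** (same section, after the preprocessing steps): "We will calculate OxyHB and deoxy-Hb at the specified time points 1–7 and regions of interest". No separate or unfiltered branch is described for these values.
- **Phases and read-outs** (Procedure; Data analysis plan). Baseline lasts 5 minutes. Then "the mother will start singing (2) and she continues singing for 3 minutes" before breastfeeding is offered. Vein search follows after a further 3 minutes or once the infant feeds well. Singing and feeding carry on until blood collection ends, and 5 more minutes are recorded after that. Read-out 2 is defined as "when the mother has started humming, approximately 2 minutes after the marker". Read-out 3 is also about 2 minutes after its marker, once feeding is established. Read-outs 1 and 7 are about 2 min 30 s after the start marker and after the end of sampling. Read-outs 4, 5 and 6 come about 30 s into the vein search, directly after puncture, and about 30 s after sampling.

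The Statistical analyses section tests the primary hypothesis, interbrain synchrony, with mixed models and wavelet transform coherence for both chromophores.

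**The concern.** A high-pass at 0.01 Hz passes fluctuations with periods shorter than about 100 s and suppresses slower ones. The phases to be compared last about 180 to 300 s. A rise or fall in oxygenation that begins with singing and persists is exactly the kind of component this filter removes, and the read-outs come late enough for the removal to be nearly complete. The filter and the read-out times are each reasonable alone; together they do not measure a sustained level.

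Read-outs 2 and 3 are the planned observations of singing and breastfeeding before the needle, and read-out 7 is the later of the two recovery observations. If singing or feeding shifts cortical oxygenation and holds it there, the contrast with baseline is largely gone before it is measured. A flat profile across these points would come from the filter but could be reported as absence of a haemodynamic effect.

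**Working it through.** The article gives no figure of its own for this point, so there is none to reproduce.

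**Inputs from the article.** Band-pass 0.01–0.5 Hz with linear detrending; sampling rate 5–10 Hz (5 Hz used); the phase lengths and read-out times above.

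**Assumptions.** Filter type and order are not stated, so several were tried. Vein search was set at 60 s, blood collection at 120 s, and read-out 5 at 5 s after puncture. The true response is a unit step smoothed by a gamma-shaped haemodynamic response.

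**Step 1: first-order check.** The time constant is τ = 1/(2π × 0.01) = 15.9 s. The share of a sustained step that remains after t seconds is exp(−t/τ):

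- t = 30 s: exp(−30/15.9) = 15%
- t = 120 s: exp(−120/15.9) = 0.05%
- t = 150 s: exp(−150/15.9) = 0.008%

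**Step 2: protocol timeline.** Baseline 0–300 s, singing from 300 s, breastfeeding from 480 s, vein search from 660 s, puncture at 720 s, end of collection at 840 s. The read-outs then fall at 150, 420, 600, 690, 725, 870 and 990 s.

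**Step 3: simulation.** The signal was detrended and band-passed with Butterworth filters of order 1–4 zero-phase, order 1–2 causal, and an FFT brick-wall. The unfiltered value of each sustained change is 1.00.

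| Simulated change | Read-out | Value left after filtering |
|---|---|---|
| Singing | 2 | −0.03 to 0.03 |
| Breastfeeding | 3 | −0.03 to 0.02 |
| Recovery | 7 | −0.03 to 0.00 |
| Singing or feeding, held to end of collection | 4 and 5 | −0.02 to 0.01 |
| Same, after it has ended (true value 0) | 6 | −0.22 to +0.13 |
| Recovery | 6 | 0.07 to 0.20 in size, sign depends on the filter |

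Causal filters of order 3 and 4 were run as well. Order 3 stays within about 1% at read-outs 2, 3 and 7. Order 4 gives −0.06 at read-outs 2 and 3 and −0.01 at read-out 7. At read-out 6 these two filters widen the artefact to about +0.30 and +0.33.

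The onset transient does pass, with a peak of about 0.34 to 0.72 of the true change, but it has gone before the 2-minute read-outs.

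**Step 4: would a lower cut-off do?** At 0.001 Hz, τ = 159 s and exp(−120/159) = 47% remains for a first-order filter; over the filters tried the share was about 23–62%. The attenuation is smaller but still large and dependent on the filter.

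**The case against.** The strongest reply is that the primary analysis is untouched. Coherence works on oscillations within the band, and 0.01–0.5 Hz preserves them. That stands. A reader might infer that the test of interbrain synchrony is invalidated; the document does not support that, and the proposal here keeps the band for coherence.

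Second, only a plateau is removed. Fluctuations with periods under about 100 s pass, and the Procedure describes changing stimulation, with singing adapted to the infant's cues. This also stands: the read-outs are in-band fluctuation around zero rather than exactly zero, and a value can be derived. It just does not measure a sustained level.

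Third, it is tempting to count four of seven read-outs as lost and to treat 4–6 as sound. Neither holds. Read-out 1 is the reference, so a value near zero there is harmless. The split from points 4–6 is not clean either, since sustained singing or feeding responses are also about zero at 4 and 5 and read-out 6 carries an artefact.

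Fourth, the Statistical analyses section sets out no explicit test of haemoglobin level against baseline, and an article may leave the use of these values to a fuller plan. So it cannot be said that the trial will report a false null. But the cut-off, the phase lengths, the read-out times and the calculation at points 1–7 are all fixed in the article, and the calculation follows the filter in the same paragraph. A fuller plan that repeated these choices would have the same fault. The averaging window is unstated, but a window centred at 2 to 2.5 minutes would not recover the change.

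**Conclusion.** The point holds for the Oxy-Hb and Deoxy-Hb level read-outs. As written, about 0–3% of a change sustained through the phase survives at read-outs 2, 3 and 7, and up to about 6% with the wrong sign under a causal fourth-order filter. Sustained singing or feeding responses are also about zero at read-outs 4 and 5, and read-out 6 is contaminated by an amount and sign that depend on the filter. The level contrast with baseline is largely removed before it is measured, so a null there would be uninformative about sustained activation.

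The result rests on the response being sustained, and on the levels being taken from the filtered signal, which is what the article describes. For read-outs 2, 3 and 7 it does not depend on the filter type or on the assumed search and collection times. It does not extend to the wavelet-coherence synchrony analysis.

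**What to change.** Separate the two uses of the signal.

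1. Keep 0.01–0.5 Hz for the coherence analysis only.
2. For the Oxy-Hb/Deoxy-Hb levels, add a branch with motion correction and low-pass filtering but without the 0.01 Hz high-pass.
3. Express responses 2 and 3 as the mean over a fixed, pre-stated window minus the mean of a short window immediately before the marker. Anchor the breastfeeding window on established feeding, which is what the Data analysis plan targets; a window just after marker 3 would catch only the start.
4. Reference read-out 7 to the end of sampling (marker 6), because marker 7 is the end of recording. Use read-out 1 only as the reference, because nothing is recorded before marker 1.
5. If the high-pass is kept for the levels, state that the values at read-outs 2, 3 and 7 do not measure sustained activation and that a null there will not be interpreted as no haemodynamic change.

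The cost is wording and one extra processing branch on stored recordings, with no new data; analysis is scheduled for 2028. The real downside is more residual slow drift in the levels, above all in the infant, since short channels are stated only for the mother's montage. A reference window close to the marker limits this drift but does not remove it.
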